## Abstract

**Background:**

In the United States certain minority groups, such as racial/ethnic immigrant women, are less likely than non-Hispanic White women to be screened for cervical cancer. Barriers to such care include health insurance, cost, knowledge, attitudes, health literacy, and cultural norms and practices. Among the most promising approaches to increase screening in these groups are patient navigators that can link women to sources of appropriate care. Another recent promising approach is using human papilloma virus (HPV) self-sampling. In this manuscript, we describe our National Cancer Institute-sponsored study testing such approaches among immigrant minority women.

**Design:**

The South Florida Center for the Reduction of Cancer Health Disparities (SUCCESS) is conducting a three-arm randomized trial among Hispanic, Haitian, and African American women in Miami-Dade County. Community health workers (CHW) based in each of three communities are recruiting 200 women at each site (600 total). Eligibility criteria include women aged 30–65 years who have not had a Pap smear test in the last 3 years. Prior to randomization, all women undergo a standardized structured interview. Women randomized to public health outreach, Group 1, receive culturally tailored educational materials. Women in Group 2 receive an individualized comprehensive cervical cancer CHW-led education session followed by patient navigation to obtain the Pap smear test at community-based facilities. Women in Group 3 have the option of navigation to a Pap smear test or performing HPV self-sampling. The primary outcome is self-report of completed screening through a Pap smear test or HPV self-sampling within 6 months after enrollment.

**Discussion:**

SUCCESS is one of the first trials testing HPV self-sampling as a screening strategy among underserved minority women. If successful, HPV self-sampling may be an important option in community outreach programs aimed at reducing disparities in cervical cancer.

**Trial registration:**

Clinical Trials.gov # NCT02121548, registered April 21, 2014.

## Background and rationale

Cervical cancer disproportionately affects women of color. In 2010, the cervical cancer incidence rate per 100,000 was 9.8 for Black women and 9.6 for Hispanic women versus 7.2 for White women [1]. The cervical cancer mortality per 100,000 women was 3.9 for Blacks and 2.6 for Hispanics versus for 2.1 non-Hispanic women [1]. In Florida, 67% of Black women presented with cervical cancer at an advanced stage versus 49% of White women [2]. Cervical cancer is also a highly preventable cancer. Cytological screening (Papanicolaou smear or Pap smear test) among women aged 21 to 65 years every 3 years or for women aged 30 to 65 years substantially reduces cervical cancer incidence and mortality [3]. With such enhanced public health promotion efforts, the vast majority of women in the United States (US) now have cervical cancer screening at least every 3 years [4]. As a result, since 2000, cervical cancer mortality and incidence have been decreasing and racial and ethnic disparities have narrowed [1].

Despite these gains, approximately 50% of cases of cervical cancer are diagnosed in women who have not been screened for more than 5 years. Further, not all women have benefited equally from these gains and certain groups remain vulnerable. Most at risk are immigrant women, including Latinas, Caribbean Blacks, and certain Asian subgroups. As an example, nationally among Latina immigrants, 70% had not completed a Pap smear test in the last 3 years [5]. Haitian women are particularly vulnerable with only 44% of such women having a Pap smear test in the last three 3 years [6]. These rates are substantially lower than the national cervical cancer screening rates of 87% [4]. Important risk factors for not being screened are immigration status, lack of insurance, length of time in US, language, and low levels of acculturation [4–6]. Additionally, among some minority and immigrant groups, socio-cultural perceptions of health, preferences for non-traditional health modalities, and historical distrust of outsiders also plays a role in screening disparities [6].

To date, one of the most promising approaches to increase cancer screening in this population has been using community health workers (CHWs). CHWs, also known as lay health workers, are community members without formal health care education who serve as a link between patients and providers to promote health among groups traditionally lacking adequate health care. A few well designed studies have found that CHWs are effective at increasing screening rates [7, 8]. However, the absolute increase is modest with an average median increase of 10 percentage points over baseline screening rates in the target communities [9].

Thus, there is a need for additional novel strategies to increase screening in these groups. One promising approach builds on the role of detection for the presence of carcinogenic strains of the human papilloma virus (HPV) as part of cervical cancer screening [10, 11]. Nearly all cases of cervical cancer are the result of infection with oncogenic strains of the HPV. Until a few years ago, HPV detection was primarily used for reflex testing of women whose Pap smear test results were indeterminate (atypical cells of unclear significance, i.e., ASCUS). Subsequently, in 2012, the US Preventive Services Task Force (USPSTF) recommended concomitant use of HPV screening with Pap smear cytology for cervical cancer screening among all women. Then, in 2014, an FDA advisory committee unanimously recommended that the HPV test using polymerase chain reaction (PCR) could be used as the initial test for cervical cancer screening [12].

One particular characteristic of HPV testing that makes it important as a tool to reach underserved women is that women can self-collect their own swabs without having to undergo a traditional pelvic exam. A recent meta-analysis found that the sensitivity and specificity of self-collected HPV samples were similar to clinician-collected samples when samples were analyzed using PCR-based testing and only slightly lower when using signal amplification-based assays [13]. Another study among Mexican women showed that self-testing was as effective as cytology screening even when scaled up in large populations [14]. Thus, increasingly, HPV self-sampling is being recommended as an important strategy to reach women not currently being screened. In the US, studies have also shown the feasibility of this approach as an outreach strategy for underserved women [15, 16]. However, whether this approach is superior to standard outreach methods, such as public health education campaigns or approaches using CHWs, is unclear.

### Objectives

To address this gap in knowledge, our study objective is to conduct a randomized trial that seeks to examine the effectiveness of a CHW-led outreach strategy that includes HPV self-sampling at increasing Pap smear screening among minority women who are not up to date on their Pap smear testing. This approach is being compared to standard public health outreach using culturally-tailored health education brochures and to a CHW-led outreach intervention that includes individualized patient navigation to health care facilities providing low cost screenings.

## Methods

### Participants, interventions, and outcomes

#### Overview and trial design

Our study is a randomized controlled trial of 600 women in three communities in Miami-Dade County (South-Dade, Little Haiti, and Hialeah). Minority women, aged 30 to 65, who have not completed a cervical cancer screening in the past 3 years and who agree to participate in the study have a 30-minute intake visit by one of our two bilingual research assistants (RA). Once they complete our research intake survey, they are randomized into one of three possible interventions. The public health outreach group receives culturally tailored cervical cancer health education materials and brochures indicating locations where low cost Pap smear screening is available (Group 1). The second group undergoes a comprehensive CHW outreach intervention that includes home visits and patient navigation to help women obtain low cost Pap smear screening in their community. The third group receives the comprehensive CHW intervention and the opportunity to have home HPV self-sampling at the time of visit. The primary outcome is self-reported cervical cancer screening (either Pap smear test or via self-sampled HPV screening) determined at a 6-month follow-up assessment done by a RA blinded to study allocation.

#### Conceptual approach

Conceptually, the design of our intervention is theoretically grounded on contemporary models specifically designed to facilitate the design and understanding of successful interventions to reduce disparities in health care among diverse communities [17]. The critical focus of such approaches is that persons reside within a community and not as patients in a healthcare system. Thus, critical for success of an intervention is linking persons in underserved settings with effective health care delivery. Equally important in our approach is the use of principles of community-based participatory research. This strategy has emerged as one of the most promising frameworks towards reducing health disparities [18]. In SUCCESS, our two key community partners are: 1) Health Choice Network of Florida (HCN), which includes two Federally Qualified Health Center (FQHCs) systems, and 2) the Center for Haitian Studies. In the study, these community partners are full participants in all phases of the project including the conception, design, conduct, interpretation of findings, and dissemination of results. Through several face-to-face meetings and conference calls, the community partners had substantial input in the study design including: 1) selection of geographic sites, 2) design of the CHW interventions (recruitment approach, conduct of home visits), 3) evaluative metrics (inclusion of measures of satisfaction and access to care), 4) ethical issues (all participants are offered HPV self-sampling at the end of their study participation), and 5) dissemination strategies (presentations to their boards, lay summaries in their newsletters). In addition, the intervention is being delivered by the CHWs, who are hired and based in these organizations rather than at the academic health center. Nearly half the research budget is allocated to these partners.

#### Study setting

For the study, the target communities we chose reflect the ethnic diversity in Miami-Dade. One is Little Haiti; Florida is home to more than a third of all Haitians in the US and Miami has the highest concentration of Haitians in the state. Little Haiti, in the northern section of Miami, has an estimated 200,000 Haitians. Most are recent immigrants who are low income, have limited formal education, and restricted access to the formal healthcare system. In addition, given their double minority status (Black and Kreyol speaking), the integration of Haitians is often slower and more challenging than that of other immigrant groups. In Little Haiti, we are working with the Center for Haitian Studies, one of the community’s leading social service organizations, which also operates a community-based healthcare facility. Our second community is Hialeah which is a separate city within Miami-Dade County. This city includes over 200,000 residents of which 94% self-identify as Hispanic and 62% of which are Cuban. As suggested by HCN, in Hialeah, we are working with Citrus Health Network Inc., the largest FQHC in Hialeah. The third target area is the southern portion of Miami-Dade county (South-Dade) which is much less urban than the above two communities. This is a very mixed landscape, including areas closer to the city composed of large low-rise public housing complexes, factory and industrial warehouses, and further out more rural agricultural areas with a large proportion of migrant farm workers. The area is also very ethnically diverse including large multi-ethnic enclaves of Latinos and Blacks, including some Haitians. In this community, we are working with Community Health of South Florida Inc. This is a FQHC network that includes several facilities and serves as the major provider of healthcare services to medically indigent residents in southern Miami-Dade County.

In each community, we are working with community advisory boards (CABs) composed of residents who represent organizations focused on health issues and socio-economic services. The CABs also include individuals who are cancer survivors and relatives or friends of persons who have been stricken with cancer. The CABs meet approximately every two months and these groups have been influential in identifying strategies for recruitment of study participants.

### Eligibility criteria

#### Inclusion criteria

To be eligible, women must be living in one of the three target communities and self-identify as Haitian, Hispanic, and/or Black. They must be aged 30 to 65 years old and not have had had a Pap smear test in the last 3 years. Women under 30 years of age have a high false positive HPV rate due to transient HPV infections. Thus, the HPV test is not recommended for women under 30 years old.

#### Exclusion criteria

A woman is not eligible to participate in the study if she i) reports having had a hysterectomy, ii) has a history of cervical cancer, iii) plans to move out of the neighborhood during the next 6 months, or iv) is currently enrolled in any other cancer prevention/outreach related study.

### Intervention

#### The CHWs

In all three arms of our study, participants are initially identified for participation and receive the intervention with the assistance of our three study CHWs. All three CHWs in the project had some experience as outreach workers but did not have any formalized health care degrees or training. All of the CHWs reflect the ethnic and racial representation of their assigned community: two are Hispanic and one is Haitian. They completed two weeks of training using modules that covered core CHW competencies [19, 20], cancer education and outreach [21], cervical cancer and HPV, and cancer clinical trials [22]. They also completed the University of Miami-required courses on human subject protections and HIPAA training using the Collaborative Institutional Training Initiative [23].

#### Intervention Group 1 – Public health community outreach

As part of our overall efforts aimed at reducing cervical cancer disparities, CHWs in each targeted community have been engaged in public health outreach. These activities include cervical cancer education campaigns over local ethnic radio stations and articles in local ethnic newspapers. The CHWs have also developed health education materials, such as brochures and fact sheets, which they distribute at events such as health fairs, community events, and other such gatherings. These are primarily based on existing materials from the National Cancer Institute (NCI) as well as other sources, such as the American Cancer Society. With feedback and suggestions from our CABs and health educators, these materials are tailored and adopted to the local culture, characteristics, and language of each community. The materials include information about the Pap smear test, why it is important, existing healthcare sources in each community, and how to go about making appointments for a Pap smear. In our study, women randomized to Group 1 are given copies of these brochures at the end of the initial intake visit. They are told the material has information on cervical cancer screening and they are encouraged to read the material. At 3 months these women also receive a brief phone call for continuity and retentions purposes reminding them of the study, obtaining any updated contact information and reminding them that at 6 months they will be called to schedule a follow-up visit by the RA.

#### Intervention Group 2 – CHW individualized health education and patient navigation

Each participant randomized to this arm receives a one-to-one health education session of approximately 1 hour. If randomized to this group, CHWs contact participants to schedule the session at a mutually convenient location. With input from professionally trained health educators and our clinical partners, the study group developed an evidence-based implementation guide as a model for conducting one-to-one health education sessions. The intervention strategies involve three overlapping domains: i) health education on cervical cancer screening, ii) motivation to encourage women to complete screening, and iii) navigation to access screening services. Study guidelines emphasize the importance of CHW judgment as to content and delivery to tailor the approach for each woman and her unique circumstances. The session begins with introductory comments followed by probing question to help individualize the intervention. Probing questions begin with generalized inquiries about what each woman knows about Pap smear tests to more targeted items asking about reasons for not having Pap tests. Based on the answers, the CHW decides how to target the intervention strategy. The CHW guide also suggests courses of action based on potential participant responses for each to consider as examples. For some women, the CHWs may need to spend time providing basic health education including explaining basic anatomy and concepts about cancer and screening, such as the relationship of early detection to reducing cancer-related mortality. For others, the discussion may also include an expanded discussion of the relationship of HPV to cervical cancer risk. This is facilitated with education materials the CHW adapts from our existing materials or other NCI resources, including anatomical graphics, brochures, and flipcharts.

#### Navigation

In addition to health education, a major role for the CHW is to offer women practical assistance that would facilitate her access to screening services. Navigation services may range from explanation of services offered at our participating clinical sites, availability of sliding fees and specific programs for cervical cancer screening for the uninsured (such as the Center for Disease Control early detection breast and cervical cancer screening programs), and assistance with making/scheduling the clinical appointments for the participant. On a case by case level, CHWs may provide assistance with other issues such as transportation (bus routes), potential language, cultural, or even child care issues, and, if requested, accompany the woman to screening appointments. CHWs also make appointment reminder calls the day prior. Within 2 weeks after a woman has the Pap smear screening, CHWs will contact the participant by phone to see if she requires any further assistance. If patients have not been notified of the results, with patient consent, the CHW tries to obtain the information from the FQHC and, with provider approval, may relay findings to the patients (all sites use electronic records). CHWs also play an important role by ensuring that each woman understands her test results. She may also provide further navigation by assisting with additional follow-up as needed, such as for colposcopy (available at each of our sites).

#### Intervention Group 3: HPV self-sampling option

Women randomized to this arm receive the same health education session as Group 2. In addition, the education includes information on HPV self-sampling as an alternative screening method. They receive an offer of choosing between the HPV screening at the conclusion of the educational session or navigation services to a traditional Pap smear test at a local healthcare facility. If the woman chooses the HPV self-sampling strategy, the CHW provides detailed instructions to complete the sample collection. Using standardized operating procedures and study-specific visual aids and flipcharts we developed, they teach women the proper self-sampling collection technique. Women complete the test in a bathroom while the CHWs wait outside to answer any questions that may arise during the process.

We are using the HPV self-sampling device developed by Preventive Oncology International and the National Institutes of Health, which is a nylon swab 2 cm in diameter and 15 cm in length. Based on prior feedback on comfort and ease of use from earlier study participants, we are using the sampler without the outer sheath. After the woman collects the sample using the swab, she removes the swab out of her vagina and gives it to the CHW. The CHW puts the swab in a pre-labeled liquid media vial (ThinPrep, Holigic Inc., Bedford, MA, US) stirs the sample, caps the bottle, and stores the sample in a re-sealable plastic bag in a locked cabinet. Once a week, the CHW delivers the samples to the University of Miami’s Department of Pathology for processing. The sample is then sent to an outside CLIA approved laboratory (Quest Diagnostics Inc.) for HPV testing. Initially our specimens were being processed by Quest using the Cervista HPV Invader Assay (Holigic In.) [24]. This was later changed to APTIMA HPV Assay (GenProbe Inc.). The former tests for HPV using a DNA based two-step signal amplification method and the latter tests for mRNA using a three step transcription-mediated amplification assay [25]. Both assays test for the 14 HPV strains which have been identified as high risk HPV by the International Agency for Research on Cancer [26] (i.e., 16, 18, 31, 33, 35, 39, 45, 51, 52, 56, 58, 59, 66, 68). They have similar sensitivities for detection of cervical intra-epithelial neoplasia (CIN2+) [27].

After the specimen is collected, the CHW asks the woman a few additional questions concerning her experience with the procedure, including ease of use, perceived correctness of device use, degree of pain associated with use, and willingness to recommend the device to family or friends as an alternative to Pap smear testing. The CHW also stresses the importance of seeing a health care provider to address any other health issues she identified during their conversations. The CHW also advises the woman that a positive result (i.e., positive for HPV high risk), will require follow-up up to ensure she receives recommended medical care. In rare cases where a submitted sample is deemed as quantity not sufficient by the laboratory, CHW will ask the woman to undergo a second HPV sampling.

#### Primary outcome

The primary outcome is self-report of completion of a Pap smear or HPV test since the initial evaluation. We will assume that women who were lost to follow-up (no further contact) did not complete a cervical cancer screening. However, participants successfully contacted by phone but who declined in-person follow-up evaluation are asked if they completed a Pap smear or HPV test. Data obtained from this phone call will be included in a sensitivity analysis on our primary outcome.

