#### Follow-up evaluation at 6-months

At 6 months, a RA blinded to study group allocation does a 6-month follow-up evaluation. The visit takes place in an area of mutual agreement with the woman. Up to 10 phone calls are made to the patient at different times and days, including weekends, to try to contact them to schedule the appointment. If the participant cannot be reached, attempts will be made using the other contact information that was provided during study intake or follow-up phone calls. If after 2 months the RA has been unable to schedule the appointment, in most cases, participants will be considered as lost to follow-up. However, in some cases the interval may be extended. This may occur if, for example, a participant was out of the country for a few months but had planned to return.

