#### Statistical analysis

All data will be analyzed using the intent-to-treat principle and we assume that women who were lost to 6-month follow-up did not have any screening. Initially, we will perform an explanatory data analysis; visually via graphics/plots, such as scatter and box-whisker plots, and numerically by descriptive statistics, such as range, median, means, and standard deviations, for measurements taken on a continuous scale. Percentages and various types of cross-tabulations will be performed for measurements taken on a categorical scale. Corresponding confidence intervals for means and proportions will also be calculated. To have a better understanding of the relationships among different study measurements, parametric or non-parametric correlation coefficients, bivariate, and multidimensional cross-tabulations, scatter, and box-whisker plots will be constructed. Prior to analyses, baseline differences of key covariates from each arm will be examined with respect to our primary outcome, particularly those related to socio-economic status. We will also examine differences on key variables between participants who completed the study and lost-to-follow-up. Analysis of variance for differences in means and *χ*^2^ test for difference in proportions will be used to test the differences among the three study arms. Several univariate and multivariate logistic regression models will be used to calculate odds ratios and corresponding 95% confidence intervals for exploring the result of having had Pap smear screening and the relationship to various types of key study covariates. Two-way interaction terms between various study variables and the study arms will also be included in the models. Standard diagnostic tools will be used to assess model fit. Transformations of the continuous data in order to meet statistical assumptions will be undertaken when indicated. We will treat primary and secondary outcomes as separate clusters, setting a 0.05 level of significance to the primary outcome. A Bonferroni correction will be applied to secondary outcomes. All statistical analyses will be carried out using SAS® version 9.3 or later for Windows (Cary, NC, US) and/or the R project for Statistical Computing for Windows (http://www.r-project.org/).

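### A screening report given by phone by a woman who declines the 6-month visit has no stated value in the primary analysis, and the two tests for loss to follow-up can leave her scored as unscreened

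*Protocol article*

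**What the plan says.** The Primary outcome section gives the definition: "The primary outcome is self-report of completion of a Pap smear or HPV test since the initial evaluation". It does not require the report to be made in person. The Overview and trial design section adds that the outcome is "determined at a 6-month follow-up assessment done by a RA blinded to study allocation".

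Three statements then bear on women without a 6-month visit.

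- Primary outcome, on women who are lost: "We will assume that women who were lost to follow-up (no further contact) did not complete a cervical cancer screening". The same section goes on to women who were reached: "participants successfully contacted by phone but who declined in-person follow-up evaluation are asked if they completed a Pap smear or HPV test". Their answers are assigned to a sensitivity analysis: "Data obtained from this phone call will be included in a sensitivity analysis on our primary outcome".
- Follow-up evaluation at 6-months: "If after 2 months the RA has been unable to schedule the appointment, in most cases, participants will be considered as lost to follow-up". The interval may be extended in some cases, for example when a participant is abroad.
- Statistical analysis, on how lost women are scored: "we assume that women who were lost to 6-month follow-up did not have any screening". This rule stands beside the commitment to intention-to-treat.

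**The concern.** The women at issue are not missing. They were reached and answered the question that defines the primary outcome. Scoring an unknown outcome as unscreened is a common convention in screening trials. Scoring a reported screen as unscreened is misclassification.

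If that happens, the primary result depends on willingness to be visited as well as on screening. Study contact differs by arm by design: Group 1 receives brochures and a brief 3-month call, while Groups 2 and 3 receive an education session with navigation or the self-sampling option. Acceptance of a further visit could therefore differ by arm. Equal declining would dilute both planned contrasts, and unequal declining would bias them.

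**Working it through.** **Step 1: follow one woman through the text.** She answers the phone, declines the visit and says she had a Pap smear.

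| Section | Test applied | Her status |
|---|---|---|
| Primary outcome | Lost means no further contact | Not lost, so the unscreened rule does not reach her. Her answer goes to a sensitivity analysis and no primary value is stated |
| Follow-up evaluation at 6-months | No appointment scheduled after 2 months, usually | Lost on the plain wording, which makes no exception for a woman who was reached |
| Statistical analysis | Lost to 6-month follow-up is scored unscreened | Unscreened if the scheduling test governs; unspecified if the no-contact test governs |

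Two definitions of lost conflict. The Statistical analysis section reuses the term and attaches the imputation without saying which definition applies.

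**Step 2: size.** The plan has no figure for this group, so there is none to reproduce. The total of 600 is not in dispute. It cannot be rebuilt from the text, which gives no Group 1 rate, clustering parameter or allocation ratio.

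Inputs from the Sample size section: differences of 20 points (Group 2 versus 1) and 15 points (Group 3 versus 2), at a 0.05 level. Assumptions: true screening of 30%/50%/65%; 200 women per arm; two-sided test; no clustering adjustment; all other women followed up; phone-only women screened at their arm's rate.

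If a fraction f of an arm is phone-only and scored unscreened, the observed rate is p × (1 − f). With equal f in all arms, each difference shrinks by (1 − f), whatever the base rates.

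- Equal f = 10%: rates 27.0/45.0/58.5; differences 20 × 0.9 = 18.0 and 15 × 0.9 = 13.5 points.
- Equal f = 5%: differences 19.0 and 14.25 points.
- Equal f = 20%: differences 16.0 and 12.0 points.
- f = 5%/5%/15%: rates 28.5/47.5/55.25; Group 3 minus Group 2 = 7.75 points.
- f = 5%/15%/5%: rates 28.5/42.5/61.75; Group 3 minus Group 2 = 19.25 points.

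**Step 3: power for Group 3 versus Group 2.** With the pooled normal approximation, power = Φ{[d − 1.96 √(2p̄(1 − p̄)/n)] / √[(p₂(1 − p₂) + p₃(1 − p₃))/n]}.

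- Phone answers counted (50% versus 65%, n = 200): (0.150 − 0.0969)/0.0489 = 1.09, power 86.1%.
- Equal f = 10% scored unscreened (45% versus 58.5%): (0.135 − 0.0979)/0.0495 = 0.75, power 77.3%.
- Equal f = 5%: 81.9%. Equal f = 20%: 67.4%.

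For Group 2 versus Group 1, power moves from 98.5% to 96.6% at f = 10%, so the Group 3 contrast is the more exposed.

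**The case against.** The strongest reply is that the plan foresaw this woman. It asks her the question and prespecifies a sensitivity analysis, so both results would be seen, and the proposal only exchanges which one leads. That much is true of the data collected. It leaves open how she is coded in the analysis that decides the trial.

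A second reply appeals to consistent measurement. The Overview ties the outcome to a blinded assessment, and the Discussion warns that self-report may overstate Pap screening by nearly 30 percentage points and says consistency of assessment was prioritised. That argument explains the choice of self-report over medical records. It does not separate phone from in-person self-report. The article does not say who asks the question by phone; if it is the same blinded assistant, blinding is unaffected.

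Third, the follow-up section mostly describes women who cannot be reached, and its rule is qualified as holding in most cases. This is fair: the authors may not have had decliners in mind. The wording still covers them.

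Four stronger readings are tempting and are not supported:

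- That three sections give three different statuses. Only two definitions of lost conflict.
- That these women are dropped from the analysis. No section says so, and the intention-to-treat statement points the other way.
- That every decliner will be scored unscreened. The text permits this without fixing it.
- That the bias runs against Group 3. The direction is unknown, as the two unequal examples show.

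**Conclusion.** The point holds as an inconsistency in stated rules for the primary outcome. It is not a detail left to a document that was not shown: the article says where the phone answer goes and gives two tests for loss that disagree about this woman. The consequence is that a reported screen can be counted as no screen in the primary intention-to-treat analysis.

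The size is unknown because no phone-only rate is given. On the stated assumptions, an equal 10% costs 2.0 and 1.5 points on the two contrasts and about 9 percentage points of power for Group 3 versus Group 2 (86.1% to 77.3%). Modest imbalance between arms matters more and can act in either direction. The formula takes declining as unrelated to screening within an arm; if screened women decline more often, the loss is larger. The rule should be settled, but nothing here shows that the result will be materially wrong.

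**What to change.** Use one definition of lost in the Primary outcome, Follow-up evaluation at 6-months and Statistical analysis sections: no screening report by visit or phone by the closing date. When the visit is declined, take the phone self-report as the primary outcome value. Impute unscreened only where no report exists. Make the in-person-only analysis the sensitivity analysis.

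The phone answers are already being collected, so no new data are needed. There are two small costs. The first is a mixed mode of collection, which the in-person-only analysis checks. The second is timing: the Data monitoring section describes primary-outcome interim analyses every 6 months, and Trial status reports 582 of 600 women enrolled, so the rule would change after interim looks. It should therefore be made as a dated amendment, with that timing stated, before the final analysis.
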